### Recruitment

Participant recruitment began in October 2021 and is expected to be completed in November 2021. We will recruit participants at the First People’s Hospital of Kunshan affiliated with Jiangsu University, Kunshan, Jiangsu Province, China. Once recruited, researchers will provide guidance on how to use the MiniApp.

### Assignment of interventions: allocation

#### Sequence generation

In this randomized controlled trial, participants will be randomized into either intervention or control arm with an allocation ratio of 1:1. The allocation will be generalized by the establishment of EDC Trial Data clinical trials centralized randomization system. Researchers will enter the system with account numbers and passwords. A randomized number generated by inputting patient information will be used to track each patient.

#### Concealment mechanism

Allocation concealment will be guaranteed through the following mechanism. Staff will log in to the EDC Trial Data cloud and enter the information for the participants. The EDC Trial Data system will randomly assign participants to either group in a 1:1 ratio. A patient profile will be generated after the necessary baseline information has been entered. Account number and password are required when assessing data.

### Assignment of interventions: blinding

Participants and investigators will be aware of the intervention that has been assigned to them in this open-label trial. Because of the nature of the patient-reported outcome measures, not all outcome evaluations will be blinded. During the analysis, the statistician will be blinded to the allocation. The procedure for unblinding is not applicable as this is an open-label trial.

### Data collection and management

#### Data collection

Data will be collected utilizing EDC at study site. Data collection takes place at seven points: baseline, day 1, day 14 (± 2), day 28 (± 2), day 56 (± 2), day 84 (± 2) during intervention period, and day 42 (± 2) post-partum. Collected data will be stored in the form of an electronic case report form. The clinical research coordinator (CRC) will complete the electronic case report form. The investigators will be informed of any changes made by CRC and system/edit check automatically done by the system. Authorized investigators will be permitted to access the study computers and evaluate the data throughout the study. If any missing data is detected via the EDC system, the researcher will contact the participants on the telephone.

#### Data management

Study teams have a responsibility to self-monitor study processes and data. This self-monitoring can ensure a well-run trial and to identify and mitigate issues before they are identified by monitoring entities, which can result in time-consuming fixes. Internal monitoring includes monitoring for proper informed consent documentation/records, eligibility criteria, and data quality. Monitoring is usually conducted by interested parties involved in the research to identify issues and to improve processes.

A unique identification code will be generated when analyzing data to ensure security. Errors or missing data information will be sent to data managers (DM) in data query reports. DM receiving the inquiry will check the original records to determine the correction. Original paperwork and signed informed consent forms will be stored in locked file cabinets.

#### Confidentiality

Personal information will be collected, shared, and maintained following ICH GCP.

### Statistical methods

#### Statistical methods for primary and secondary outcomes

Categorical variables will be expressed in numerical values with their respective percentages and compared using the chi-squared test at baseline. Continuous variables will be expressed as mean ± SD and compared using the *t*-test. The significance of primary and secondary endpoints will be evaluated with the paired-samples *t*-test. A *p*-value < 0.05 indicates statistical significance. All data will be analyzed with the SPSS.

All patients who have received CBT for at least 4 weeks will be included in the full analysis set (FAS). Depending on the time investigated, the per-protocol (PP) analysis set will be made up of patients who complete the 6-month follow-up examinations. The FAS will be used as the basis for the primary analysis. If there is a discrepancy of greater than 10% between the FAS and PP samples, the analysis will be repeated for the PP analysis set. The safety population will include patients in the FAS. Unless otherwise noted, all analysis will be done in both the FAS and PP analysis sets. No additional analysis will be conducted.

There will be no replacement or imputation of missing values. All analysis will be based solely on observed cases. Patients who loss to follow-up will be considered to have dropped out of therapy. Only the PP patients will be used in a sensitivity analysis to test the impact of this assumption.

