**Methods:**

This trial is designed as a prospective randomized controlled trial, which enrolled the patients diagnosed with GDM in First People’s Hospital of Kunshan affiliated with Jiangsu University from September 2021 to March 2023 with a 3-month follow-up. The specific randomization method was established and implemented through the central randomization system of EDC clinical trials. The percentage of all blood glucose levels collected within the normal range between the two groups at baseline, during the intervention period, and postpartum infant and maternal outcomes will be measured. Summary statistics for continuous variables will include the number of subjects, mean, median, SD, or the standard error, minimum, and maximum. The chi-square test, *t* test, and paired-sample *t* test were used for statistical analysis of differences between groups.

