### Sample size

Considering the primary outcome variable as the difference in the percentage of blood glucose within normal range between two groups, an absolute difference of 10% in the percentage of blood glucose within normal range is expected. Power was set at 0.8, the one-sided significance level at 0.05, and the confidence interval (CI) at 95%. Eighty subjects per group were calculated according to a 1:1 ratio of random grouping. A total sample size 100 was needed in each group that to account for an additional 20% in attrition size.

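### No planned between-arm comparison uses the baseline in-range percentage; an ANCOVA on a pre-intervention baseline would repair the paired test and recover precision

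*Protocol article*

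**What the plan says.** The statistical methods section of the protocol article names three tests. Categorical variables are compared at baseline by chi-squared test. For the rest, "Continuous variables will be expressed as mean" ± SD, with a t-test. On the endpoints it states: "The significance of primary and secondary endpoints will be evaluated"; the test it gives for this is the paired-samples t-test. No model with a covariate appears. Missing values are not imputed and only observed cases are analysed.

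The abstract says the trial will measure the percentage of glucose values "within the normal range between the two groups at baseline, during the intervention period" and after delivery. The data collection section lists a baseline time point separate from day 1. The primary outcome section, however, describes glucose monitoring only after enrolment, from randomisation (day 0) to week 12. The inclusion criteria require a completed OGTT at 24–28 weeks.

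The sample size section gives the target effect: "an absolute difference of 10% in the percentage of blood glucose within normal range is expected". For the error rates it takes 80% power, with "the one-sided significance level at 0.05". The resulting size is 80 evaluable women per arm under 1:1 allocation, raised to 100 per arm "to account for an additional 20% in attrition size". It states neither an SD nor a control-group level.

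**The concern.** The primary hypothesis concerns a difference between two randomised groups. The test assigned to it is paired. If the pairs are each woman's baseline and follow-up values, the test uses baseline but answers a within-arm question. If the pairs are women across arms, there is no pairing to exploit and baseline is not used. Either way, baseline does not enter a comparison of the arms.

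The obvious repair is an independent two-sample t-test. It is valid, but it stops short: any share of the outcome variance that baseline explains stays in the error term. The trial is sized at 80% power with a one-sided 5% level and so has little to spare. A repair by comparing raw change scores could be worse than no adjustment at all if r is low.

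**Working it through.** **Inputs from the sample size section:** difference 10 points, power 0.80, one-sided alpha 0.05, 80 evaluable per arm, 20% attrition. **Assumed, because the documents do not give them:** that the sizing compared two means, the SD, and r.

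**1. The plan's own figures.** Attrition reproduces: 80 / (1 − 0.2) = 100 per arm. The 80 cannot be reproduced without an SD, so I solve backwards with the normal approximation:

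SD = 10 × √(80/2) / (1.645 + 0.842) = 63.25 / 2.487 ≈ 25.4 points.

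A noncentral-t calculation gives 25.3. If the sizing had been two-sided, the implied SD would be 22.6. Reading the sizing as a comparison of two proportions does not fit well: 80% versus 90% needs 157 per arm one-sided, and a figure close to 80 arises only at 90% versus 100% (77 one-sided with continuity correction, 74 two-sided without). The two-mean reading is therefore the more plausible one, but it remains an assumption.

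**2. Unadjusted comparison.** SE = 25.44 × √(2/80) = 4.02, and 10 / 4.02 = 2.486. One-sided power is Φ(2.486 − 1.645) = 0.80, by construction. Two-sided power is Φ(2.486 − 1.960) = 0.70.

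**3. Adjusted comparison.** ANCOVA reduces the SD to SD × √(1 − r²). A change-score analysis has SD × √(2(1 − r)). With 80 per arm:

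| r (assumed) | Variance removed by ANCOVA, r² | ANCOVA power, one-sided | ANCOVA power, two-sided | n per arm for 80% one-sided | Change-score power, one-sided | Change-score power, two-sided |
|---|---|---|---|---|---|---|
| 0 | 0% | 0.80 | 0.70 | 80 | 0.55 | 0.42 |
| 0.3 | 9% | 0.83 | 0.74 | 73 | 0.68 | 0.56 |
| 0.5 | 25% | 0.89 | 0.82 | 60 | 0.80 | 0.70 |
| 0.7 | 49% | 0.97 | 0.94 | 41 | 0.94 | 0.89 |

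Example at r = 0.5: SE = 4.02 × √0.75 = 3.48; 10 / 3.48 = 2.871; Φ(2.871 − 1.645) = 0.89; Φ(2.871 − 1.960) = 0.82. The 95% CI half-width falls from 1.96 × 4.02 = 7.9 to 1.96 × 3.48 = 6.8 points.

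**4. Why the paired test does not do this job.** Suppose both arms improve by the same 5 points, so there is no treatment effect. In one arm of 80, the paired statistic has mean 5 / (25.44 × √(2(1 − r)) / √80). At r = 0.5 this is 5 / 2.844 = 1.758, and the chance of p < 0.05 (two-sided, in the direction of improvement) is Φ(1.758 − 1.960) = 0.42. At r = 0.3 and 0.7 the chance is 0.32 and 0.62. A significant paired result therefore says nothing about the difference between arms.

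**5. Is there a usable baseline?** The abstract says yes for the in-range percentage. The body starts monitoring after enrolment and defines no pre-intervention window. Values recorded after allocation could already reflect treatment, since the trial is open-label and the intervention is most intensive in weeks 1–3. An OGTT, in contrast, is required before entry for every woman.

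**The case against.** The strongest objection is that an unadjusted comparison of randomised arms is valid, that covariates are often left to an analysis plan that is not shown, and that the size of the gain rests on two quantities the documents do not contain. Validity is conceded. But the article does not leave the endpoint test open: it names one, and that test does not compare the arms. Since the sentence has to be rewritten anyway, the replacement is worth choosing well. That the size of the gain is conditional stands in full: at r = 0.3 it is only 3 points of one-sided power, and a short baseline window or a single OGTT value may well give a low r.

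A reader might infer several stronger things that the documents do not support:

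- That the primary analysis ignores baseline altogether. On its natural reading a paired test uses baseline, only not to compare arms.
- That the statement that no additional analysis will be done forbids a covariate. It closes the paragraph on analysis sets and does not clearly reach the main model.
- That HbA1c and the self-efficacy score have baseline values. Both are listed as outcomes without a visit schedule, and the timeline figure is not shown.
- That adjustment is entirely free. With observed cases only, an ordinary ANCOVA drops any woman without the covariate.
- That the 70% two-sided figure is caused by lack of adjustment. It comes from sizing one-sided and then testing two-sided, which is a separate matter.

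**Conclusion.** The point holds as a recommended improvement to the analysis, tied to the paired-test sentence. As written, no planned comparison of the arms uses baseline, and a plain two-sample t-test would correct the validity fault without using the precision that a baseline value offers.

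On the assumed two-mean sizing with an SD of about 25 points and 80 per arm, ANCOVA raises one-sided power from 80% to about 83% (r = 0.3) or 89% (r = 0.5), and two-sided power from 70% to 74% or 82%. With r near zero there is almost no gain. The conclusion that ANCOVA is at least as precise as the unadjusted test for any appreciable r does not depend on the assumed SD; the power figures do. All of it requires a covariate fixed before the intervention starts, and for the in-range percentage that rests on the abstract alone.

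**What to change.** - Replace the paired-samples t-test for the primary endpoint with an ANCOVA of each woman's in-range percentage over the 12 weeks, with arm as factor and a pre-intervention baseline as covariate. Report the adjusted difference between arms with its 95% CI.
- Define the covariate before analysis: the baseline in-range percentage if it is recorded before the intervention starts, and otherwise a pre-randomisation glucose value such as one from the OGTT required for entry. Do not use monitoring values collected after allocation.
- Use the same model for HbA1c and the self-efficacy score where a baseline value is collected.
- State a simple rule for women who lack the covariate, for example filling in the mean of both arms combined, and exempt baseline covariates from the no-imputation sentence so that these women are not dropped.

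The cost is a few sentences of analysis text. SPSS, the software already named, fits the model. If the OGTT value serves as covariate, no further data are needed. If the baseline percentage is preferred and is not recorded before the intervention, data collection would have to change.

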### Objectives

Aim 1: To determine the efficacy in treating hyperglycemia of mobile-based CBT interventions in GDM patients, compared with conventional face-to-face interventions.Hypothesis 1a (primary study hypothesis): a significant difference in the percentage of blood glucose levels within a normal range is expected between the two groups. The normal range is defined as fasting blood glucose.

Aim 2: To determine the efficacy of mobile-based CBT interventions in infants and maternal outcomes, compared with conventional face-to-face interventions.Hypothesis 2a: a significant difference in the variables evaluating infants and participants outcomes, including low-birth-weight neonates, neonatal macrosomia, events of hypoglycemic events in infants, and cesarean delivery, is expected between two groups.

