### Trial design

This study is a single-center, randomized, controlled, open-label parallel-group superiority trial. Patients will be randomly allocated at a 1:1 ratio to evaluate the efficacy of CBT to lower blood glucose in GDM patients. The study protocol follows the Standard Protocol Items: Recommendations for Interventional Trials (SPIRIT) [16].

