#### Secondary outcome measures

1) The percentage of blood glucose levels collected within the normal range on each selected examination day.2) Loss of self-monitoring rate.3) HbA1c.4) Mean score of Diagnostic and Statistical Manual of Mental Disorders (DSM-5) assessment. DSM–5 is developed as a standard classification system for mental disorders. It provides a guideline of structured clinical interviews utilized to diagnose depression [18]5) Mean score of General Self-Efficacy Scale (GSE). The GSE is a psychometric scale that measures the confidence in one’s capacity to deal with a wide range of life’s issues. The test consists of ten items that describe attitudes toward barriers and are assessed on a scale of 0 (least optimal) to 4 (very optimal). A version in Chinese translation has been approved [19]6) Any insulin dose prescribed.7) Case number of low-birth-weight neonates. Low birth weight is defined as the first weight recorded after the birth of less than 2500 g (up to and including 2499 g) [20]8) Case number of neonatal macrosomia. Neonatal macrosomia is defined as the first weight recorded after the birth of more than 4000 g (more than and including 4000 g) [21].9) Hypoglycemic events in neonates (blood glucose < 2.2 µmol/L).10) Other fetal adverse events.11) Case number of GDM comorbidity developed during the intervention period.12) Case number of cesarean delivery.13) Total expenditures for delivery.

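### The endpoint tests are wrongly and inconsistently assigned: a paired-samples t-test is named for a comparison of two independent randomised arms, including birth outcomes that have nothing to pair

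*Protocol article*

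**What the plan says.** The protocol's Statistical methods section makes three assignments in sequence.

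- Categorical variables: "Categorical variables will be expressed in numerical values with their respective percentages and compared using the chi-squared test at baseline".
- Continuous variables: "Continuous variables will be expressed as mean ± SD and compared using the" t-test, with no time point or endpoint attached.
- Endpoints: "The significance of primary and secondary endpoints will be evaluated with the paired-samples" t-test. No secondary endpoint is exempted.

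The section adds that there will be no further analyses.

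The abstract names the chi-square, t and paired-sample t tests together and says of the three that the "test were used for statistical analysis of differences between groups". It does not say which test serves which endpoint.

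The design is a "single-center, randomized, controlled, open-label parallel-group superiority trial" with 1:1 allocation. The primary hypothesis is that "a significant difference in the percentage of blood glucose levels within a normal range is expected between the two groups". Hypothesis 2a is likewise a difference between groups, in birth and delivery outcomes. The Sample size section is built on a 10-point difference between groups. Neither matching nor crossover is described.

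**The concern.** A paired t-test needs two values from the same woman, or from a matched pair. Applied before versus after within an arm, it asks whether that arm changed. Applied across the arms, it would need a pairing of unrelated women that the design does not supply. Neither use tests the difference between randomised groups on which both hypotheses rest.

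The problem is sharpest for birth outcomes. Items such as "Case number of cesarean delivery" are recorded once per woman and have no earlier value. The one test in the plan that would suit them, chi-squared, is tied in the statistical section to baseline.

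The stakes are practical. The control arm also receives lifestyle education, so both arms may improve. A significant within-arm change would then say little about the app. With conflicting descriptions, the choice of confirmatory test could also be made after the data are seen.

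**Working it through.** **Step 1. Tests against endpoints.**

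| Endpoint | Values per woman | Test named in the statistical section | Can it compare the arms? |
|---|---|---|---|
| Percentage of readings in range (primary) | Many after enrolment; a baseline value is mentioned only in the abstract | Paired t | No: within-arm change only |
| Low birth weight, macrosomia, neonatal hypoglycaemia, caesarean delivery | One, binary | Paired t (chi-squared only at baseline) | No: no paired difference exists |
| Delivery expenditure | One, continuous | Paired t | No: no paired difference exists |

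**Step 2. The plan's own figure.** The attrition step reproduces: 80 / (1 − 0.20) = 100 per group. The base of 80 cannot be reproduced, because no SD is given. Treated as a comparison of two independent means (10 points, 80% power, one-sided 0.05), it implies

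SD = 0.10 × √(80/2) / (1.645 + 0.842) ≈ 0.254.

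This SD is back-solved and serves only as an assumption in Step 4. The point does not depend on it.

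**Step 3. What within-arm testing would do, if efficacy were read that way.** Assumptions: no true difference between arms, 80 women per arm, two-sided 0.05 (the plan's threshold is p < 0.05 with the side not stated), and both arms improving by d standard deviations of the within-woman change. Let p be the power of one paired t-test, from the non-central t distribution with 79 degrees of freedom and non-centrality d√80. The arms are independent, so

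P(significant in CBT, not in control) = p(1 − p).

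| d | p | p(1 − p) |
|---|---|---|
| 0 | 0.050 | 4.8% |
| 0.10 | 0.143 | 12.3% |
| 0.22 | 0.494 | 25.0% (maximum) |
| 0.25 | 0.598 | 24.0% |
| 0.30 | 0.755 | 18.5% |
| 0.40 | 0.942 | 5.4% |
| 0.50 | 0.993 | 0.7% |

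**Step 4. Check by simulation.** Inputs: 5,000 trials per row, 80 per arm, identical arms, assumed SD 0.254 and assumed within-woman correlation 0.5. The SD of the change is then 0.254 × √(2 × (1 − 0.5)) = 0.254, so shifts of 5 and 10 points are about 0.20 and 0.39 SD.

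| Common shift | Paired t in CBT arm rejects | Significant in CBT only | Independent t-test rejects |
|---|---|---|---|
| 0 points | 5.2% | 4.9% | 4.9% |
| 5 points | 41.5% | 24.2% | 4.8% |
| 10 points | 93.9% | 6.5% | 5.1% |

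The independent t-test holds its 5% level whatever the shared shift. The paired test responds to the shift itself.

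**The case against.** The strongest reply is that between-group tests are present in the document. The abstract attaches all three tests to group differences. In the statistical section, the words limiting a test to baseline belong to the chi-squared sentence only, so the t-test sentence can be read as covering continuous endpoints. This reply has force: a reader might infer that, followed as written, the plan never tests Hypotheses 1a and 2a, and the documents do not support so strong a reading. What remains is that the sentence dealing specifically with endpoint significance names the paired test. The abstract labels the paired test as between-group too, so it adds to the conflict and does not resolve it.

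A second reply concerns size. Nowhere does the protocol say that efficacy will be judged by significance in one arm and not in the other, and the common shift is assumed. A reader might double the 24% to about 48% and set that against 5%. That figure counts trials favouring control as well, and 0.25 SD lies close to the worst case, so it should not be used.

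Third, it is tempting to argue for ANCOVA by its gain in power. The documents give neither an SD nor a correlation, and glucose monitoring is described as starting after enrolment. Only the abstract's "The percentage of all blood glucose levels collected within the normal range between the two groups at baseline, during the intervention period" suggests a baseline percentage in range. No specific gain can be claimed, and an independent-samples test is enough to cure the error.

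**Conclusion.** The point holds as a wrong and contradictory test assignment, and it should be corrected before analysis. The test named for endpoint significance does not fit an unmatched parallel-group comparison and cannot be formed for outcomes that occur once. This follows from the text alone and needs no numerical assumption.

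The size is conditional. If efficacy were read from within-arm tests, a false finding in favour of CBT would arise in at most 25% of trials under the Step 3 assumptions, and in well under 5% once the shared improvement reaches 0.50 SD. An actual false-positive rate for this trial cannot be given, because the protocol does not state that rule.

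**What to change.** Replace the paired-test sentence in the Statistical methods section with wording along these lines:

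- The per-woman percentage of readings in range, and the other continuous endpoints, are compared between randomised arms by an independent-samples t-test. Where a suitable covariate measured before randomisation exists (for example the entry OGTT value), ANCOVA with that one pre-specified covariate may be used. The mean difference is reported with its 95% CI.
- Binary birth and delivery outcomes are compared between arms by a chi-squared or Fisher's exact test, with the risk difference and 95% CI.
- Paired tests, if kept, describe change within each arm and carry no inference about efficacy.

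State for each endpoint which of these applies, choose between the t-test and ANCOVA before the data are seen, and bring the abstract into line. The same edit should say whether p < 0.05 is one- or two-sided, since the Sample size section uses one-sided 0.05.

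The cost is wording only. The independent-samples and chi-squared or Fisher's tests need no data beyond what is already planned, and a completed OGTT is an entry requirement. A baseline percentage in range should not be relied on as covariate unless the protocol confirms that it is collected before randomisation.

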### Interventions

To compare the effects of CBT in GDM patients, a control intervention—a conventional lifestyle intervention—will be provided. Patient education will be provided to the control group via oral communications from endocrinologists. The control group will also receive patient education, which will include disease-related knowledge, lifestyle modification, complication prevention, and other topics, but only during each follow-up.

Interventions will be delivered by WeChat MiniApp: “CBT GDM” (developed by Hangzhou Kang Sheng Health Consulting CO., LTD). This includes 5 sessions. The contents are designed and reviewed by endocrinologists and psychiatrists from the First People’s Hospital of Kunshan affiliated with Jiangsu University, Kunshan, Jiangsu Province, China. Participants will study according to a learning schedule which is divided into a strong intervention period (1–3 weeks) and a regular intervention period (4–12 months) (see Fig. 1).

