### Criteria for discontinuing or modifying allocated interventions

In the following circumstances, dropping out of the treatment program will be considered. At this point, participants will not be regarded to have dropped out of the experiment, and they will be eligible for protocol assessments unless they withdraw their consent for assessments (as described below).1) If the participant requests that the protocol treatment was discontinued.2) If the participant is unable to continue the protocol treatment due to adverse events.3) When the investigator believes that the risk of continuing the protocol treatment outweighs the benefits for any reason.4) When the investigator believes that continuing the protocol treatment is not appropriate for any other reasons.

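### The full analysis set requires at least 4 weeks of CBT and has no rule for controls, so the primary comparison and the safety population are selected on exposure after randomisation

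*Protocol article*

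**What the plan says.** The definition is in the protocol article, Statistical methods for primary and secondary outcomes: "All patients who have received CBT for at least 4 weeks will be included in the full analysis set (FAS"). The same paragraph gives the set its role, "The FAS will be used as the basis for the primary analysis", and adds "The safety population will include patients in the FAS".

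The only other set is also selected after randomisation: "the per-protocol (PP) analysis set will be made up of patients who complete the 6-month follow-up examinations". The section then states "No additional analysis will be conducted", uses observed cases without imputation, and names one sensitivity analysis, restricted to per-protocol patients.

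On the control arm, Interventions says "Patient education will be provided to the control group via oral communications from endocrinologists". On stopping treatment, Criteria for discontinuing or modifying allocated interventions says "participants will not be regarded to have dropped out of the experiment, and they will be eligible for protocol assessments", unless they withdraw consent for assessments. It lists adverse events among the reasons for stopping.

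**The concern.** A full analysis set is meant to preserve the randomised comparison. This one admits patients by how long they received one of the two treatments. That has three consequences.

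- **No rule for controls.** The criterion is stated in terms of CBT, which the control arm does not receive.
- **Selection after randomisation.** Women who stop CBT before week 4 leave the primary analysis. The trial is open-label and glucose is self-monitored, so early stopping could well be related to glucose control. If it is, the groups compared are no longer those that randomisation made alike.
- **Safety.** A woman who stops CBT in weeks 1–3 because of an adverse event falls outside the stated safety population.

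At stake are the validity of the primary estimate and its p-value, and the denominator for harms.

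**Working it through.** **1. The text, side by side**

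- Objectives, Trial design and Sample size plan a difference between two groups, 1:1, parallel, superiority, 100 per group.
- Statistical methods admits only patients with at least 4 weeks of CBT. Applied literally to 100 + 100 = 200 randomised women, this gives at most 100 CBT patients and 0 controls, so no between-group comparison is possible.
- Two repairs are conceivable: (a) all controls are kept and the rule applies to the CBT arm; (b) 4 weeks of allocated care is required in both arms. Under (a) selection acts on one arm. Under (b) it acts on both, but not necessarily alike: CBT session completion is tracked in the app, whereas controls receive education only at follow-up visits.
- Primary outcome measures fixes the window from day 0 to week 12. A 4-week criterion therefore falls inside the period being measured.
- Both planned sets are selected after randomisation, so no planned output shows what the selection did.

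**2. The plan's own figure**

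Attrition: 80 / (1 − 0.20) = 100 per group, as stated. The 80 itself cannot be reproduced, because neither an SD nor a control-arm value is given. Solving n = 2·SD²·(zα + zβ)² / Δ² for SD, with n = 80, Δ = 10 points and power 0.8:

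- one-sided 0.05, as the article states: SD = 10 × √40 / (1.645 + 0.842) = 25.4 points
- two-sided 0.05: SD = 10 × √40 / (1.960 + 0.842) = 22.6 points

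**3. Hypothetical size of the bias, repair (a)**

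Assumptions that are not in the documents: no true effect; 100 randomised per arm; all controls kept; the least adherent fraction f of the CBT arm removed; adherence and outcome bivariate normal with correlation ρ; SD 25.4.

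- Bias = SD × ρ × φ(z_f) / (1 − f), with φ(z_f) / (1 − f) = 0.1755 / 0.9 = 0.195 for f = 0.10 and 0.280 / 0.8 = 0.350 for f = 0.20.
- SE = SD × √(1/[100(1 − f)] + 1/100) = 3.69 for f = 0.10 and 3.81 for f = 0.20.
- Two-sided type I error = 1 − Φ(1.96 − bias/SE) + Φ(−1.96 − bias/SE).

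| f | ρ | Bias (points) | Bias/SE | Two-sided type I error |
|---|---|---|---|---|
| 0.10 | 0.3 | 25.4 × 0.3 × 0.195 = 1.5 | 0.40 | 0.07 |
| 0.10 | 0.5 | 25.4 × 0.5 × 0.195 = 2.5 | 0.67 | 0.10 |
| 0.20 | 0.3 | 25.4 × 0.3 × 0.350 = 2.7 | 0.70 | 0.11 |
| 0.20 | 0.5 | 25.4 × 0.5 × 0.350 = 4.4 | 1.17 | 0.21 |

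Simulation with an independent-samples t-test agrees (0.07, 0.10, 0.11, 0.22).

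**4. Sensitivity**

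- With SD 22.6 the biases scale by 22.6/25.4, to about 1.3 to 4.0 points. Type I error is unchanged, because SD cancels in bias/SE.
- At the one-sided 0.05 level of the sample-size section, the case f = 0.20, ρ = 0.3 gives 1 − Φ(1.645 − 0.70) = 0.17.
- A weaker link gives less: at f = 0.05 and ρ = 0.1 the bias is 0.3 points and one-sided type I error 0.06.

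**The case against.** The strongest reply is that the sentence is loosely drafted and its intent is clear: two arms are to be compared, so controls must be in. That stands. A reader might infer that the trial will analyse no controls, but the two-group design stated in Objectives, Trial design and Sample size makes a drafting slip far more likely. The reply does not remove the exposure criterion.

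Several other inferences are tempting and go further than the text allows.

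- **That early stoppers leave one arm only, and that the result favours CBT.** This holds only under repair (a), with non-adherers doing worse. If both arms had equal exclusion and equal correlation, the bias would be zero. The direction is assumed, not documented.
- **That the discontinuation section is contradicted.** It keeps treatment stoppers available for assessment and is silent on analysis sets. Collecting their data and then leaving them out sits badly with that section, but is not a strict contradiction.
- **That the analyst must be unblinded.** The blinding section says "the statistician will be blinded to the allocation". The article has app tracking and separate data managers, either of which could supply a membership flag. It does not say who builds the set.
- **That early harms vanish.** Adverse event reporting and harms has any adverse event reported to the national centre, with no link to the full analysis set. What is affected is the stated safety population.
- **That the size is known.** The SD is back-solved, the stopping rates and correlations are assumed, and the article's 20% is overall attrition, not stopping before week 4. The illustration also uses an independent-samples test, whereas the article names a paired-samples t-test for its endpoints.

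Nor can the point be left to an analysis plan: the article states a definition, and nothing else in it corrects that definition.

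**Conclusion.** The definition is wrong as written and must be changed. It gives controls no route into the primary analysis, and under either plausible repair the comparison still depends on exposure after randomisation, with no all-randomised analysis to check it against. That conclusion rests on the text alone and needs no numerical assumption.

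The size is illustrative. If the rule acts on the CBT arm alone and stopping is moderately related to outcome, the distortion is roughly 15% to 44% of the 10-point target (1.5/10 to 4.4/10), with two-sided type I error of about 0.07 to 0.22 instead of 0.05. It could be smaller, larger or nil under other assumptions. The safety population as stated also omits women who stop CBT before week 4, although their events would still be reported.

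**What to change.** Replace the analysis-set text with wording to this effect:

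- **Full analysis set:** all randomised participants, analysed in the arm to which they were randomised, regardless of treatment received or its duration. Use all observed glucose data and report by arm the number without any post-baseline reading. The primary analysis uses this set.
- **Safety population:** all randomised participants in both arms.
- **Per-protocol set:** move the 4-week CBT exposure rule here, with an equivalent attendance rule for controls.

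The cost is small. Assessment after stopping treatment is already provided for, so no new data collection is needed. Because the plan uses observed cases without imputation, a woman with no post-baseline reading contributes no endpoint value, which is why that count by arm has to be reported. The estimated effect may be slightly smaller than among adherers.
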